#### Quality of life (QoL)

By understanding the subjective perception of the impact of bladder symptoms on the quality of life (38), it can reflect the severity and efficacy of neurogenic bladder symptoms. By asking the patient, “What do you think if you continue to have the same urination symptoms for the rest of your life?” According to the patient’s satisfaction with the current urination symptoms, the answer was: 0: happy; 1: Satisfaction; 2: Generally satisfied; 3: It’s OK; 4: not satisfied; 5: Distress; 6: It’s bad. The higher the score, the worse the patient’s quality of life.

### Statistical analysis

All data will beanalyzed using SPSS 21.0 statistical software. The measures will beexpressed as mean ± standard deviation (
$\bar{x}$
±SD), and one-way analysis of variance (ANOVA) or chi-square test will be used in all demographic characteristics and baseline assessments, The primary and secondary outcome measures will be expressed as 
$\bar{x}$
±SD, and the data will be tested for a normal distribution. Before and after treatment, the uniformity of variance data between the two groups will be analyzed using *t* test. If the data is skewed, it will be converted to normal distribution according to the data distribution type; If the data does not conform to any distribution law, the rank sum test will be used to test the hypothesis of the data. Data with abnormal distributions or uneven variances will be analyzed using Wilcoxon rank sum tests. *X*^
**2**
^ test was used for counting data, and *p* < 0.05 for all tests was considered statistically significant.

The fNIRS data will beprocessed by professional data analysts of Wuhan Ired Medical Equipment Co., LTD. SPSS 21.0 will beused for data analysis to calculate the differences in activation intensity of each brain region, and the average concentration changes of HbO2, HbR, and HbT in each channel of subjects in each group will becalculated. Paired sample *t* test will beused to investigate the differences in blood oxygen changes before and after treatment, and one-way analysis of variance will be used for comparison between groups. *p* ≤ 0.05 will beconsidered as a statistically significant difference.

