**Method/design:**

This is a single-center pilot RCT, which 60 patients with urinary retention after SCI will be selected, numbered in chronological order of hospitalization, and randomly divided into 4 groups using the random number table method, Groups A (control group), Group B, Group C, and Group D; Each group will receive the same conventional rehabilitation treatment. The whole intervention period 2 weeks and will be evaluated before and after treatment to collect data on residual bladder volume, functional near-infrared spectroscopy (fNIRS), changes in voiding condition, changes in surface electromyography (SEMG) values of pelvic floor muscle and quality of life scores (QoL).

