### Sample size calculation

According to published literature (33) the mean post-intervention residual urine volume in the four groups A, B, C, and D were expected to be 302.6, 56, 107.2, and 179, respectively, with a standard deviation of 160.4. The degree of certainty 1−β = 0.90, test level *α* = 0.05, group A:B:C:D = 1:1:1:1 and sample size estimation will be performed using PASS 15 software according to the following equation.

$$n=\Psi^{2}\left[\overset{k}{\underset{i=1}{\sum }}{s_{i}}^{2}/k\right]/\left[\overset{k}{\underset{i=1}{\sum }}{\left({\bar{X}}_{i}-\bar{X}\right)}^{2}/\left(k-1\right)\right]$$

According to the predefined parameters, the minimum required samples for groups A, B, C and D were all 12 cases after the calculation of residual urine volume using One-Way Analysis of Variance F-Tests under the Means menu of PASS 15 software. Considering the lost rate of 20%, it is expected that 15 cases will be included in groups A, B, C, and D in this study, and a total of 60 cases will be included, which can ensure the accuracy and scientific accuracy of the study results.

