### Primary outcome

The most important evaluation index is the residual urine volume of the bladder, the residual urine volume of the bladder can intuitively show the improvement of the urination function of patients with urinary retention. The main way is to measure the residual urine volume of the urinary system color ultrasound of the four groups of patients on the first day of treatment and the first day after treatment. Prior to the examination, the patient first attempts to empty the urine without external force or manipulation, and then a urinary ultrasound will be performed immediately. During the examination, the patient will be asked to lie flat on their back with the probe located in the midline above the pubic symphysis. Each measurement will scan the bladder in both the sagittal and transverse planes and measure the bladder capacity at this point to get an idea of the patient’s residual urine volume. The smaller the residual urine volume, the lower the degree of urinary retention.

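### The primary outcome of this four-arm trial is assigned a two-group test at an unadjusted 0.05, which does not match the one-way ANOVA F-test used to size the trial

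*Protocol article*

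**What the plan says.** According to the abstract, patients are "randomly divided into 4 groups using the random number table method": A sham, B bilateral M1, C S3 nerve root, D both sites. On the primary outcome, the Primary outcome section says: "The most important evaluation index is the residual urine volume of the bladder".

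The Sample size calculation section plans for a single test. It takes post-treatment means that "were expected to be 302.6, 56, 107.2, and 179, respectively, with a standard deviation of 160.4", sets alpha 0.05 and power 0.90, and obtains 12 per arm "using One-Way Analysis of Variance F-Tests under the Means menu of PASS 15 software". A 20% loss allowance brings this to 15 per arm, 60 in all.

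The Statistical analysis section then assigns the tests:
- Demographic and baseline data: one-way ANOVA or chi-square.
- Primary and secondary outcomes: "Before and after treatment, the uniformity of variance data between the two groups will be analyzed using" a t test, with the Wilcoxon rank-sum test where distributions are abnormal or variances unequal.
- fNIRS: a paired t test for before versus after, and "one-way analysis of variance will be used for comparison between groups".
- Level: p < 0.05 "for all tests was considered statistically significant".

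**The concern.** The t test and the rank-sum test each compare two groups. This trial has four, hence six possible pairs, and the section refers to two groups without saying which. ANOVA appears for baseline data, for fNIRS and for sizing, but not for residual urine volume.

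Two things are at stake. The first is the error rate: several two-group tests, each read at 0.05, do not hold 5% across the claim they jointly support. The second is the link to the sample size: the 5% and 90% in the Sample size calculation describe the overall F-test and do not carry over to pairwise t tests.

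The comparisons the trial cares about can be read from its hypothesis and objectives. Whether magnetic stimulation works concerns A–B, A–C and A–D. Central versus peripheral, and combined versus single-site, concern B–C, B–D and C–D. Together these are all six pairs, in two families of three.

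**Working it through.** **Inputs.** Means 302.6, 56, 107.2 and 179 mL, common SD 160.4 mL, alpha 0.05, power 0.90, equal allocation and 20% loss, all from the Sample size calculation. The per-test level of 0.05 is from the Statistical analysis section. Sidedness is not stated; two-sided is assumed.

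**1. The plan's own figure.** The grand mean is (302.6 + 56 + 107.2 + 179)/4 = 161.2. The squared deviations sum to 19,993.96 + 11,067.04 + 2,916.00 + 316.84 = 34,293.84. The noncentrality is λ = n × 34,293.84 / 160.4² = 1.333n, with 3 and 4(n − 1) degrees of freedom.
- n = 11: power 0.879
- n = 12: power 0.910
- n = 15: power 0.965

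So 12 per arm is the minimum, and 12/0.80 = 15. The sample size reproduces and is not in question.

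**2. False-positive rate of unadjusted t tests.** Four normal arms with equal means and variances were simulated (200,000 replicates), each pair tested by a two-sided t test at 0.05. The table gives the chance of at least one significant result.

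| Tests | 12 per arm | 15 per arm |
|---|---|---|
| A–B, A–C, A–D | 12.5% | 12.5% |
| B–C, B–D, C–D | 12.2% | 12.1% |
| All six pairs | 20.3% | 20.2% |
| Overall F-test alone | 4.9% | 4.9% |

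With rank-sum tests on all six pairs the rate is 18.9% (12 per arm, 20,000 replicates). Treating tests as independent would give 1 − 0.95³ = 14.3% for three and 1 − 0.95⁶ = 26.5% for six; these are too high because pairs share arms. In about 15% of null trials at least one of the six pairs is significant while the F-test is not.

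**3. Power of the pairwise t tests at the planning means.** For a pair, noncentrality = difference / (160.4 × √(2/n)). At n = 12 the denominator is 65.48, with 22 degrees of freedom.

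| Pair | Difference (mL) | Noncentrality | Power at unadjusted 0.05 |
|---|---|---|---|
| A–B | 246.6 | 3.77 | 0.949 |
| A–C | 195.4 | 2.98 | 0.814 |
| A–D | 123.6 | 1.89 | 0.439 |
| B–D | 123.0 | 1.88 | 0.435 |
| C–D | 71.8 | 1.10 | 0.182 |
| B–C | 51.2 | 0.78 | 0.116 |

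Only A–B reaches 90%. None of the active-versus-active pairs reaches even 50%.

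**The case against.** The strongest reply is that the key sentence is badly worded rather than a deliberate plan. It can be read as before versus after, as arm versus arm, or as both. The fNIRS paragraph separates these properly, and the authors use ANOVA elsewhere, so ANOVA may have been meant here too. That is plausible, and it limits what can be inferred about intent. It does not rescue the text. Read as arm versus arm, the test compares two groups out of four. Read as before versus after, no between-arm test of the primary outcome is named. If ANOVA was meant, the section has to say so.

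A second reply is that post-hoc procedures, testing order and multiplicity corrections are often left to an analysis plan, which is not shown. That stands: their absence alone is not the point. The point is what the article does fix, namely a two-group test and a flat 0.05, at odds with its own sample size section.

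A third is that this is a pilot. That mitigates little, because the trial is sized for efficacy at 90% power and its objectives include showing clinical effectiveness and comparing sites.

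A reader might also infer that the false-positive risk for the main claim is simply 20%, with any of six comparisons able to confirm that stimulation works. The documents do not support that. They list no pairs, and a difference between two active arms says nothing about stimulation versus sham.

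**Conclusion.** The defect holds in this form: the protocol names no four-group test for its primary outcome, and the two-group test it does name, at an unadjusted 0.05, is not the test that the trial was sized on. If pairs are compared as written, the familywise false-positive rate is about 12% for the sham comparisons, about 12% for the comparisons among active arms, and about 20% only if all six are tested and pooled. These figures assume no true difference, normal data with equal variances, and two-sided tests. The 90% power applies to the overall F-test alone. The sample size of 12, inflated to 15 per arm, is correct for that F-test. The passages need to be reconciled before the data are analysed.

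**What to change.** In Statistical analysis, name one-way ANOVA on post-treatment residual urine volume at 0.05 as the primary test, matching the Sample size calculation. Make the six pairwise comparisons with Tukey, or Games-Howell if variances differ, at 5% familywise and with 95% confidence intervals. Give any before/after comparison its own sentence. In Sample size calculation, state that 0.05 and 90% refer to the overall F-test.

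If a contrast of the mean of B, C and D against A is wanted, test it only after a significant F-test and label it supportive. Added as a further ungated test at 0.05, it would raise the null error to about 0.079 beside the F-test, or 0.074 beside F-gated Tukey (12 per arm).

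No patients are added. The cost is pairwise power at the planning means with 12 per arm:
- A–B from 95% to about 86%, or about 85% if Tukey is read only after a significant F-test
- A–C from 81% to 62%
- A–D from 44% to 23%
- at least one of the six pairs from 98% to 90%

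The overall F-test keeps its 91%.

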**Objective:**

(1) To illustrate the clinical effectiveness of FMS in the treatment of urinary retention after SCI and to provide a new treatment modality for the patients; (2) Comparison of the differences in the efficacy of central and peripheral single FMS and combined central and peripheral FMS in the treatment of urinary retention after SCI; (3) To explore the central control mechanisms of bladder function recovery after SCI in conjunction with changes in fNIRS.

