#### Functional brain imaging techniques

In this study, we will collecte the fNIRS data with a 37-channel device (BS-3000, Wuhan Zilian Hongkang Technology, Wuhan, China), and will use BrainScope software to display and save the fNIRS data. The data will be processed by Wuhan Yiride Medical Equipment Co., LTD, and the average concentration changes of oxy-hemoglobin (HbO2), Deoxy-hemoglobin (HbR) and Total- hemoglobin (HbT) in each channel of subjects in each group will be calculated. Before the experiment, the patients will be asked to sit in a chair, and the light source and detector will be placed on the head and close to the scalp of the patients. The signals will be mainly collected in the primary motor area (M1), pre-motor area and auxiliary motor area, in which channel 19 will beused as the Cz reference point, and the left and right cerebral hemispheres were distributed symmetrically, As shown in Figure 2. The main detection indexes were the content of HbO2, HbR, and HbT. Participants will berequired to keep quiet during the test without any movements (29). The block design was adopted: the resting period was 25 s and the task period was 15 s. Considering the need for subjects to acclimatize to the detection environment and to ensure that the fNIRS signal reaches a steady state, 25 s of baseline resting data will be collected before proceeding to the task period. The resting period and the task period will be repeat for 5 times, and then the resting data of 25 s will be collected after the end, for a total of 225 s. Resting period (25 s): 25 resting periods in which participants rest without any movement. Task period (15 s): complete the “anal lift” 3 times within 15S according to the operator’s suggestion (the “anal lift” movement is guided by the pelvic floor rehabilitation therapist before the test).

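### The fNIRS analysis sets a flat p ≤ 0.05 with no lead region, channel or haemoglobin index and no stated unit of testing, and its only before-after test makes no use of the randomisation

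*Protocol article*

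**What the plan says.** The Objective section of the protocol article gives fNIRS the task "To explore the central control mechanisms of bladder function recovery after SCI in conjunction with changes in fNIRS". Under Functional brain imaging techniques, a 37-channel device is used, and "The signals will be mainly collected in the primary motor area (M1), pre-motor area and auxiliary motor area". The same section states that "The main detection indexes were the content of HbO2, HbR, and HbT".

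The fNIRS paragraph of the Statistical analysis section describes two levels of summary. One is by region: SPSS serves "to calculate the differences in activation intensity of each brain region". The other is by channel, where the plan is that "the average concentration changes of HbO2, HbR, and HbT in each channel of subjects in each group will becalculated". The next sentence names the tests: a paired t test "to investigate the differences in blood oxygen changes before and after treatment, and one-way analysis of variance will be used for comparison between groups". The paragraph closes by setting p ≤ 0.05 as significant. It mentions no adjustment for the number of tests and no leading region, channel or index.

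Under Research group and intervention, all four groups, sham included, receive bladder care, bladder function training and acupuncture.

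**The concern.** There are two separate problems.

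**Many tests, one flat threshold.** Three haemoglobin indexes are measured at many sites, and each can be tested within arms and between arms. With nothing named in advance as leading, any significant site or index can be presented as the mechanism. Because the unit of testing is left open, it could also be chosen after the data are seen.

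**The before-after question is answered within arms.** A paired t test in an active arm shows whether that arm changed. It does not show whether stimulation caused the change. Every arm receives the same background treatment. Patients may enter from one month after injury, when recovery over time is plausible. The anal-lift task is taught before the test and repeated at the second assessment. Sham patients could change just as much.

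What is at stake is objective 3. The Discussion expects fNIRS and electrophysiology to explain how the treatment works, and it reports finding no earlier study that used fNIRS for central bladder control after spinal cord injury. By its own account, the trial has no prior fNIRS result in this setting to help tell real sites from chance ones.

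**Working it through.** **The plan's own figure.** The article gives no test count or error rate for fNIRS. Its only calculation is the sample size for residual urine volume, which reproduces. The four means (302.6, 56, 107.2, 179) have grand mean 161.2 and sum of squared deviations 34,293.84. With SD 160.4, the noncentrality at n = 12 per group is 12 × 34,293.84 / 160.4² ≈ 16.0. Power is 0.910 at n = 12 and 0.879 at n = 11, so 12 is the minimum, and 12 / 0.8 = 15 per group. This calculation does not involve fNIRS.

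**Inputs**
- Channels: 37 (Functional brain imaging techniques)
- Regions: 3, namely M1, pre-motor and auxiliary motor (same section)
- Indexes: 3, namely HbO2, HbR and HbT (same section)
- Test families: 5, that is, one paired family in each of four arms plus one between-group ANOVA family. Running the paired test arm by arm is an assumption; the text does not say so.
- Threshold: 0.05 per test (Statistical analysis)

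**Formula.** Expected false positives = number of tests × 0.05. For the paired tests this assumes no before-after change in any arm. For the ANOVAs it assumes no difference between arms.

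| Reading | ANOVAs only | Paired, four arms | Total |
|---|---|---|---|
| By region | 3 × 3 = 9 tests → 0.45 | 36 tests → 1.80 | 45 tests → 2.25 |
| By channel | 37 × 3 = 111 tests → 5.55 | 444 tests → 22.2 | 555 tests → 27.75 |

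Other readings change the count. Splitting each region by hemisphere gives 6 × 3 × 5 = 90 tests and 4.5 expected. Pooling the arms for the paired test leaves two families: 3 × 3 × 2 = 18 tests and 0.9 expected by region, or 37 × 3 × 2 = 222 tests and 11.1 expected by channel.

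**Chance of at least one false positive among the ANOVAs, if independent**
- By region: 1 − 0.95⁹ = 0.37
- By channel: 1 − 0.95¹¹¹ = 0.997

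**Effect of correlation.** Neighbouring channels are correlated, and HbT is the total of the other two indexes. A simulation used 15 patients per arm, 37 channels, HbT as the sum of HbO2 and HbR, and an assumed common correlation between channels of 0 to 0.8. The mean count over all 555 tests stayed at 27.4 to 28.1, as it must. The spread widened: the 5th to 95th percentile was 17 to 40 at correlation 0 and 1 to 91 at 0.8. The chance of at least one significant ANOVA fell from 0.99 to 0.58. Under strong correlation, false positives therefore tend to come in clusters, and a cluster can look like an activation pattern.

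**Attribution.** The paired test uses one arm's own baseline, and the sham arm does not enter it. The one-way ANOVA compares randomised arms including sham, so it can isolate stimulation. As described it has no baseline covariate, and the text does not say which quantity is compared.

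**The case against.** The article never says that tests run channel by channel. Channel averages are to be calculated, the same sentence speaks of each brain region, and the sentence naming the tests gives no unit. A reader might infer that the plan commits to 555 tests and about 28 false positives. The text does not support that as a statement of fact: 28 is the upper case of one plausible reading, and the region reading gives about 2. Nor does 37 × 3 at 0.05 give 28 by itself. It gives 5.55, and the rest comes from the four within-arm families. This part of the objection stands.

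A reader might also infer that no fNIRS change could be credited to stimulation. That goes too far, because the sentence that plans the paired test also plans a between-group ANOVA, and the groups include sham. The attribution problem is confined to the paired tests, and the article does not say that mechanism will be inferred from them alone.

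The two complaints also use different nulls. If all arms change through rehabilitation or recovery, significant paired tests reflect real change that may be wrongly attributed, not chance. Calling a third of the tests redundant because HbT is a total would likewise be too strong, since a test on a sum is not determined by the tests on its parts.

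Finally, fNIRS is a secondary, exploratory outcome in a pilot, and multiplicity handling may sit in an analysis plan that is not shown. This limits the severity but does not remove the point. The article states the tests and the threshold; it is not silent on them.

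**Conclusion.** The concern holds in a limited form. The article fixes an unadjusted p ≤ 0.05 for fNIRS, names nothing as leading, and leaves open both the unit of testing and the quantity the ANOVA compares. The total of about 2 to 28 assumes no true change and a paired test in each arm. The between-group figures of about 0.45 and 5.6 do not depend on the paired-test assumption. Correlation between channels leaves these expectations unchanged but makes the actual count much more variable.

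Independently of any count, within-arm paired tests cannot show an effect of stimulation. The between-arm comparison can, and objective 3 should rest on it. Because the outcome is exploratory, this is a change that should be made; it does not threaten the primary analysis.

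**What to change.** Settle the following before any fNIRS data are examined.

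- Make the between-arm comparison the stated basis for objective 3. Take task-related HbO2 averaged over each of the three regions already named, and compare the four arms by ANCOVA of the post-treatment value with the baseline value as covariate. Control the false discovery rate at 5% across the three regions, for example by Benjamini-Hochberg.
- Label HbR, HbT and all channel-level results exploratory, with false discovery rate control across channels.
- Report within-arm before-after changes descriptively, not as evidence of a stimulation effect.

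Leading with HbO2 and the particular multiplicity method are partly matters of choice. Another index or method would serve if named in advance.

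No new patients, visits or measurements are needed, since baseline fNIRS is already scheduled. The cost is revised analysis wording, region averaging by the existing analysts, and fewer results called significant.

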### Safety and adverse effects of rFMS

RFMS is generally noninvasive and safe, but occasionally causes transient headache and fatigue (39). Adverse events will be managed as follows: (1) If informed of discomfort, the investigator will immediately stop treatment, assess the patient’s vital signs, type and degree of discomfort, and then administer appropriate treatment. (2) All adverse events will be recorded and reported to the principal investigator and the ethics committee, who will jointly decide whether the patient is fit to continue participation.

